**Fig 1 pone.0355160.g001:**
[figure not shown]
TARGeT intervention: Protocol and procedures. The protocol consists of a preparation phase in the hospital (assessments, device onboarding), a 6-week home-based intervention where participants train using the technologies, and a follow-up phase in the clinic to assess the effects of the intervention. A) Schematic participant timeline according to the SPIRIT reporting guidelines, B) illustrative protocol overview.

Ethical approvals were obtained from the NHG Domain Specific Review Boards on 13 June 2024 (ECOS reference number: 2023/00527, protocol version 2, see S2 File) and ETH Zurich Ethic Commission on 11 March 2024 (Reference number: 23 ETHICS-342). The study will be conducted according to the Declaration of Helsinki and all participants will provide signed written informed consent to the clinical team before participation. The study was registered on ClinicalTrials.gov with the following registration number: NCT06406569 on 06 May 2024. Additionally, for personal data protection and cybersecurity, approval from Singapore’s national health tech agency, Synapxe, was obtained before the commencement of the study. Results of the study will be made available in scientific publications.

This manuscript was written in accordance with the SPIRIT (Standard Protocol Items: Recommendations for Interventional Trials) guidelines [25] (see S1 File).

With reference to pilot studies, sample sizes in the range of 10–30 participants are recommended [26]. We will therefore recruit up to 30 participants, aiming for a sample size of 25, factoring in a drop-out rate of about 20% (5 participants).

The inclusion and exclusion criteria for participants were derived from experiences in previous studies with the technologies used here [9,18,27,28].

The inclusion criteria are as follows:

Clinical stroke (ischaemic or haemorrhagic) confirmed by admitting doctors and brain imaging (computed tomography (CT), CT angiography or magnetic resonance imaging)Age 21–80 yearsAt least 28 days post-strokeUpper limb motor impairment of FMA scale [29] 20–60Montreal Cognitive Assessment (MoCA) [30] > 21/30Ability to sit supported and continuously for 60 minutesStable home abode with enough space to place technologies (clear floor area of at least 1.2m x 2.0m in the proximity of a power socket)Availability of caregiver to assist in home-based exercises

Participants will not be recruited if any of the following exclusion criteria are present:

Functional impairment of the upper limb due to other pathologies than strokeMedical conditions incompatible with research participation: uncontrolled medical illnesses (hypertension or diabetes, ischaemic heart disease, congestive heart failure, bronchial asthma, severe/untreated depression, agitation, end-stage renal/liver/heart/lung failure, unresolved cancers)Anticipated life expectancy of less than six monthsPacemakers and other active implantsActive seizures within three monthsLocal factors potentially worsened by intensive technology-aided upper-limb therapy and computer-based training:Spasticity - modified Ashworth Scale (MAS) [31] > 2 of any upper limb muscle groupsSevere pain in affected arm - Visual Analogue Scale for pain (pVAS) [32] > 5/10Skin woundsSevere visual impairment or visual neglect affecting the ability to use technologiesHistory of dementia, depression, or behavioural problemsPregnant or lactating females

After recruitment, participants may be withdrawn from the study in the following circumstances:

Poor fit to the technologies that could potentially cause complications (e.g., strain)Safety concerns (e.g., dizziness due to screen use)Serious adverse events related to the technologyNew medical problems unrelated to study intervention: recurrent stroke, new organ failure, new diagnoses rendering subject ineligibleNot complying with the study procedures

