After the home training of six weeks, the study team will retrieve the technologies and conduct another semi-structured interview with the participant to understand their perception and experience with the unsupervised TARGeT program. The Intervention phase will terminate with a post-intervention assessment (t2) in the clinic to determine the immediate effects of the therapy including clinical assessments, usability evaluations, and HrQoL questionnaires.

In the beginning of the Intervention phase, i.e., few days after the onboarding session at home, therapists will call the participants to check on their ease of use and potential problems. During the remaining Intervention phase, therapists will remotely monitor the participants’ compliance with the therapy plan at least once per week (more details in Section 5) and will contact the participants via phone call or text message in case there has been no training with the technologies on the remote monitoring website for at least two consecutive days. Additionally, participants will be given the option to contact the therapists whenever needed. Any off-protocol contact required due to, e.g., non-training or technical issues of the technologies will be recorded in dedicated report forms for feasibility, safety, and economic analysis.

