#### Follow-up phase.

The protocol will be finalized with the Follow-up phase, in which the long-term effects of the intervention will be assessed at six weeks (t3) and 18 weeks post-intervention (t4). The follow-up assessments comprise clinical assessments in the clinic, HrQoL scales, and cost questionnaires for the participants. Adverse events related to training will also be monitored at each follow up session, i.e. pVAS, MAS, skin issues etc.

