#### Technology data.

The feasibility of the TARGeT program will be assessed based on adherence to the therapy plan, which is determined by both attendance and training dose. Attendance is defined as daily access to the technologies, measured through log-in and log-out times recorded by the technologies. The daily training dose is defined by the daily active training time, i.e., the duration spent performing the exercises, excluding planned breaks. For deeper future analyses, also, the exercises played, the aggregated number of task repetitions as well as the progression of the challenge levels per technology will be stored. Depending on the technology and the exercise, also the kinematic, dynamic, and EMG data as well as pre-established performance measures (e.g., smoothness [47]) will be saved.

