#### Journal and report forms.

Stroke survivors, caregivers, therapists, and technical personnel will log the time spent on the intervention and report any interaction with the respective other parties that were not scheduled in the protocol in journal and report forms, e.g., identified by remote monitoring, as well as any safety and technical concerns encountered. From this data, the safety of the TARGeT program will be determined.

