#### Clinical scales.

The clinical upper limb status of the participants will be determined at every time point (t0 to t4) with standardized clinical scales for motor impairment (FMA and Grip strength (GS) measured by a digital dynamometer), functional performance (Action Research Arm Test (ARAT) [48], Box-and-Block Test (BBT) [49]), spasticity of the shoulder adductors, elbow, wrist, and finger flexors (MAS), and pain (pVAS).

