#### Usability scales.

To assess the usability of each technology, the System Usability Scale (SUS [50]) and the Raw Task Load Index (RawTLX [51]) will be used at the mid (t1, first technology set) and post-assessment (t2, second technology set).

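### Poor fit, safety concerns, device-related serious events and non-compliance can end participation in the study rather than only the device or training, so later supporting data may be lost from those who tolerated the program worst

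*Protocol article*

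**What the plan says.** The withdrawal rule stands in *Study design, setting and participants*: "After recruitment, participants may be withdrawn from the study in the following circumstances". Five grounds follow: poor fit to the devices, safety concerns, serious adverse events related to the technology, new unrelated medical problems, and failure to follow study procedures. The verb is permissive, and what the participant leaves is the study.

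The data that could be affected are scheduled as follows.

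- *Usability scales*: the SUS and RawTLX "will be used at the mid (t1, first technology set) and post-assessment (t2, second technology set".
- *Intervention phase*: "After the home training of six weeks, the study team will retrieve the technologies and conduct another semi-structured interview with the participant". *Data analysis* then clusters the post-intervention interviews by safety and feasibility concerns.
- *Follow-up phase*: "Adverse events related to training will also be monitored at each follow up session", with pain, spasticity and skin named as examples.
- *Clinical scales*: "The clinical upper limb status of the participants will be determined at every time point (t0 to t4) with standardized clinical scales". Quality of life is measured at t0, t2, t3 and t4, and the cost questionnaires at t0, t3 and t4.

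Two sources accrue as training proceeds, and *Outcome measures* classes both as primary. Attendance is "measured through log-in and log-out times recorded by the technologies". Of the journal and report forms the article says: "From this data, the safety of the TARGeT program will be determined".

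Non-training does not lead straight to withdrawal. After at least two consecutive days without training, therapists "will contact the participants via phone call or text message in case there has been no training with the technologies".

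**The concern.** Four of the five grounds are signs of poor tolerance or poor feasibility, which this trial sets out to measure. If they end study participation, later data go missing because the program went badly. Usability ratings, interview themes on safety, the course of device-related events and the clinical results at later visits would then come mainly from people who coped.

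The rule also sits awkwardly with the case for several complementary devices. Someone who fits one robot poorly may still be able to use the other, or MyoGuide, but the list offers no stop at device level.

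Most of what is at stake is qualitative. In a study of up to 30 people, the interview and event course of a few badly tolerated cases may tell a future trial more than a small shift in a mean score.

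**Working it through.** **1. The plan's own figure.** The article recruits up to 30 to reach 25, allowing about 20% drop-out (5 participants). 25 × 1.20 = 30, which reproduces the figure; 25 / 0.80 = 31.25 is close. As a share of those recruited, 5/30 = 16.7%. The 5 covers drop-out for all reasons, so it is an upper case for these four grounds within the planned allowance.

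**2. What withdrawal from the study would remove.** Visits are t1 (week 3), t2 (week 6), t3 (week 12) and t4 (week 24).

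| Assessment | Scheduled after baseline | Missed if withdrawn before t1 | Missed if withdrawn between t1 and t2 |
|---|---|---|---|
| Clinical scales | t1, t2, t3, t4 | 4 of 4 | 3 of 4 |
| Usability scales | t1 (first set), t2 (second set) | t1 rating of devices used | t2 rating of devices used |
| Post-intervention interview | after week 6 | missed | missed |
| Follow-up adverse-event checks | t3, t4 | 2 of 2 | 2 of 2 |
| Quality of life | t2, t3, t4 | 3 of 3 | 3 of 3 |
| Cost questionnaires | t3, t4 | 2 of 2 | 2 of 2 |

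Someone who leaves before t1 has never used the second robot at home, so a t2 rating of it is not applicable rather than lost. Someone who leaves between t1 and t2 has already rated the first set, including MyoGuide.

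**3. What survives.** Device logs up to withdrawal, the journal and report forms up to withdrawal, and the record of the triggering event.

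**4. Size of a possible shift.** Let n = 30 have started, k be withdrawn, and mS and mW be the means of those who stay and those withdrawn.

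- Mean of all = [(n − k)·mS + k·mW] / n
- Mean of stayers − mean of all = (k/n)·(mS − mW)
- k = 1: 1/30 = 3.3% of the difference. k = 3: 3/30 = 10%. k = 5: 5/30 = 16.7%.

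The documents give no value for mS − mW. The ranges below are assumptions for illustration.

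- SUS, assumed difference 10 to 30 points: k = 1 gives 10/30 = 0.33 to 30/30 = 1.00 points; k = 5 gives 50/30 = 1.67 to 150/30 = 5.00 points. This applies only to a device everyone has used, which before t1 means MyoGuide, and it requires all k to leave before t1.
- FMA, assumed difference 2.5 to 5 points: k = 1 gives 2.5/30 = 0.08 to 5/30 = 0.17 points; k = 5 gives 12.5/30 = 0.42 to 25/30 = 0.83 points.

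**5. Reach of a change.** Data collection ends on 05 June 2026. If that is the last t4 visit, 24 weeks (168 days) earlier is 19 December 2025 for the last baseline, and about 30 January 2026 for the end of that participant's six weeks. After that, an amendment can affect only follow-up visits.

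**The case against.** The strongest objection is that the loss is inferred. The article never says that visits, an exit interview or event follow-up cease on withdrawal, and a condensed article may leave such provisions to the full protocol (version 2, S2 File), which is not shown. This stands as a limit, and the point is conditional on it. It does not remove the point, because the article does print a rule, and its object is the study.

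Other objections also stand. The rule is discretionary, and non-training first prompts contact. Some poor-fit cases may surface during onboarding, before there is experience to rate, and a person who misses visits may supply no visit data under any rule. The clinical conclusions are already described in the *Discussion* as limited.

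A reader might infer three stronger things that the text does not support.

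- *That the adherence result is inflated.* If 5 of 30 left the denominator and all 25 others met a criterion, 25/25 = 100% would replace 25/30 = 83%. But the article nowhere says that withdrawn participants leave the adherence summary, and their logs exist.
- *That the safety outcome loses its events.* The triggering event is captured in the forms. What may be lost is its later course at t3 and t4 and the participant's own account in the interview.
- *That the repeated measures ANOVA would discard anyone with a missing visit.* *Data analysis* does not state how missing visits are handled, and that is commonly left to the analysis plan.

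**Conclusion.** The point holds as a weakness in how the rule is fixed. As printed, four grounds tied to poor tolerance or compliance can end study participation, and nothing in the article keeps those participants in later assessments. Using the rule would selectively remove the secondary and supporting data listed above. It leaves the primary adherence logs and the journal and report forms up to withdrawal intact.

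The size of any bias cannot be derived. The k/30 relation is exact for means, but the SUS and FMA differences are assumed, and k = 5 takes the whole planned drop-out. With one or two such withdrawals the numerical shift is small, and the loss lies mainly in the interviews and event follow-up. The conclusion assumes that withdrawal from the study has its ordinary meaning and that the full protocol makes no other provision. It is worth changing as a cheap improvement.

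**What to change.** In the withdrawal list, make poor fit, safety concerns, technology-related serious adverse events and non-compliance reasons to stop the affected device or the training only. Then state that:

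- unless they withdraw consent, these participants are invited to the remaining visits up to t4, the usability scales for devices they actually used, and the post-intervention interview;
- device-related events are followed to their outcome;
- everyone who started training stays in the safety and adherence summaries;
- participants already withdrawn are reported by reason.

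New unrelated illness, such as recurrent stroke, can remain a ground for ending clinical assessment.

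The cost is a protocol amendment with ethics review (two bodies approved the study) and a few extra visits, for which clinic attendance is already compensated. Some participants will decline. Reach is limited by the end of data collection on 05 June 2026. For those already withdrawn, reporting by reason and keeping them in the two summaries needs no new data.

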### Rehabilitation technologies

To provide a comprehensive therapy program, three rehabilitation technologies were selected that complement each other by focusing on different segments of upper limb post-stroke therapy and that are easy to use in unsupervised settings which we consider as a key requirement for home therapy. From proximal to distal, H-Man focuses on sensorimotor functions of the shoulder and elbow, ReHandyBot on the forearm and hand, and MyoGuide on the wrist and hand. All technologies comprise multiple engaging exercises for user interaction and come with intelligent algorithms that adapt the challenge level of the interaction in the exercises based on the individual performance of a user to allow for unsupervised training. Moreover, all technologies have been previously successfully evaluated in terms of usability and/or clinical benefit for stroke survivors in separate pilot trials [9,27,28].

#### H-Man.

H-Man is a table-top end-effector robotic technology that allows planar movements targeting shoulder-elbow function. It was designed at Nanyang Technological University, Singapore [33] and is commercialized by Articares Pte. Ltd. (Fig 2). Through a gamified environment, H-Man provides repetitive, performance-adaptive exercises that target relearning sensorimotor control for resuming activities of daily living while also training cognitive functions. Depending on the participant’s needs, end-effectors with different grasp modes and an arm support for gravity compensation can be provided. H-Man has been successfully employed previously in neurorehabilitation therapy and assessment of sensorimotor functions in stroke survivors [34,35]. In a recent study, H-Man was successfully tested for unsupervised use in stroke survivors’ homes [18].

**Fig 2 pone.0355160.g002:**
[figure not shown]
Technologies used in the TARGeT study. The three technologies employed at participants’ homes for daily training focus on different segments of the upper limb. From proximal to distal: H-Man on shoulder and elbow, ReHandyBot on forearm and hand, and MyoGuide on wrist and hand.

#### ReHandyBot.

ReHandyBot, which was developed by the Rehabilitation Engineering Laboratory at ETH Zurich, is a compact and portable two-degree-of-freedom end-effector robot that trains and assesses grasping movements, forearm pronation and supination [36] (Fig 2), and is a portable redesign of the ReHapticKnob [37]. It is embedded in a therapy platform proposing a set of exercises based on the neurocognitive therapy concept [38], to assess and train motor and sensory functions in the context of challenging tasks requiring cognitive processing (e.g., exploring and recognizing virtual objects with different mechanical properties rendered by the robot [39]). Exercises present different difficulty levels that are automatically adapted depending on participants’ impairment level (assessment-driven therapy) and performance during therapy [40,41]. ReHandyBot comes with a color-button keyboard that allows for easy navigation through the user interface. In previous studies with ReHandyBot and its predecessor in stroke survivors, it was shown that assessment-driven robot-assisted therapy leads to non-inferior recovery compared to dose-matched conventional care [27]. A recent feasibility study showed that minimally supervised therapy with the robot is possible and well accepted by stroke patients, with the technology showing high usability [10,24].

#### MyoGuide.

MyoGuide is a non-actuated technology for specifically training wrist extension and hand opening movements via biofeedback. Finger extension (hand opening) is a fundamental prerequisite for releasing objects and performing many activities of daily living [42], whereas sustained wrist extension provides stability for the hand during functional tasks and optimizes grasp force production [43–45]. It comprises an electromyography (EMG) armband (Myo armband, Thalmic Labs) for recording muscle activities from the forearm via eight EMG channels and a mobile device (e.g., tablet) to display the exercises and feedback [28]. The placement of the armband is not strictly defined but is recommended to be placed near the elbow to capture the extensors and flexors of both wrist and fingers. Our signal processing algorithm accommodates the armband placement and is able to derive reliable signals for game control. After user calibration tasks and technology-specific assessments, the user can engage in dynamic tasks targeting the control of wrist extension and hand opening (depending on the clinical impairment). The difficulty level of the exercise (i.e., the required muscle activation level, speed and accuracy of muscle control) is adapted based on the user’s performance. The usability of MyoGuide has recently been evaluated positively by subacute stroke survivors and their therapists [28].

#### Preparation phase in clinic.

This phase will consist of baseline assessments (t0) and two onboarding sessions for the first technology set (one for each device of the first set, e.g., MyoGuide and H-Man), conducted upon informed consent (-t1). The baseline assessment (t0) will include clinical scales, health-related quality of life (HrQoL) scales, and cost questionnaires. Details of the individual assessments are provided in Section 4.

Each onboarding session in clinic will last up to 120 minutes in which the participants will be trained in the operation of the technologies. As per advice from clinicians, participants might be jointly trained with their caregivers. The onboarding will follow a defined protocol inspired by our previous work [46] in which participants and caregivers will slowly transition from a fully supervised operation and training mode (i.e., the research therapist will instruct the participant on how to use the technology and closely observe the participant while training and interfere whenever needed), to a minimally-supervised training (i.e., the research therapist will only be available on demand).

After the second onboarding session, the clinical team will set up a therapy plan (60–90 minutes daily) for the unsupervised home training with the technologies of the first technology set. The therapy plan will allow for the automatic execution of the exercises, individually selected for the respective participant.

Onboarding sessions will not be considered as interventions with a therapeutic effect but serve to qualify participants and caregivers in the independent operation and interaction with the technologies in preparation for unsupervised training at home.

#### Intervention phase.

After the in-clinic onboarding, the first technology set will be installed at a participant’s home and a third onboarding session (up to 120 minutes) will be conducted at their home. In this session, the participant will be trained (together with the caregiver) on the safe and correct, unsupervised operation of and training with the technologies. If, after the third onboarding session, the participant and caregiver are not deemed proficient enough for unsupervised training, more onboarding sessions at home can be arranged. Also, if required, appropriate furniture for the interaction with the technologies will be provided. During the at-home onboarding visit, a semi-structured interview with the participant will be conducted to understand experiences and expectations with post-stroke rehabilitation.

The unsupervised training at home will then start with the first set of technologies for three weeks in which participants are instructed to train daily according to their therapy plan. The daily therapy plan comprises 15 minutes training with MyoGuide and 45 minutes using H-Man or ReHandyBot, with the option to extend the training to up to 120 minutes per day. This upper limit is based on clinical experience of the study team and is set to avoid excessive fatigue and injuries. It is also consistent with previous studies with unsupervised, technology-assisted therapy (e.g., [18]). The shorter duration of MyoGuide was chosen because it requires repeated, high-intensity muscle activations close to maximal EMG output, which can quickly lead to fatigue. The training can be split up into multiple sessions over the day as per the participant’s convenience. In the middle of this three-week training, participants will receive one add-on conventional therapy session in the clinic (Fig 1) to support the translation of the gained function. This session also offers the opportunity for the participants to discuss the training progress with the therapists. After completion of the three-week training with the first technology set, participants will return to the clinic for a fourth onboarding session with the remaining technology (e.g., if H-Man was part of the first set, they will be onboarded to ReHandyBot). Additionally, a mid-assessment (t1) will be performed, comprising clinical scales and usability questionnaires. Next, in an at-home onboarding session, the new actuated technology will be set up and the old will be collected. Again, the fitness for unsupervised training with the new technology will be assessed by the therapists and if needed additional onboarding sessions can be arranged. The participant will then be advised to train for another three weeks daily in an unsupervised manner with this second technology set according to the updated therapy plan (up to maximum 120 minutes daily). During this second part of the intervention, the participant will also return to the clinic for a conventional therapy session in the middle of the three weeks.

After the home training of six weeks, the study team will retrieve the technologies and conduct another semi-structured interview with the participant to understand their perception and experience with the unsupervised TARGeT program. The Intervention phase will terminate with a post-intervention assessment (t2) in the clinic to determine the immediate effects of the therapy including clinical assessments, usability evaluations, and HrQoL questionnaires.

In the beginning of the Intervention phase, i.e., few days after the onboarding session at home, therapists will call the participants to check on their ease of use and potential problems. During the remaining Intervention phase, therapists will remotely monitor the participants’ compliance with the therapy plan at least once per week (more details in Section 5) and will contact the participants via phone call or text message in case there has been no training with the technologies on the remote monitoring website for at least two consecutive days. Additionally, participants will be given the option to contact the therapists whenever needed. Any off-protocol contact required due to, e.g., non-training or technical issues of the technologies will be recorded in dedicated report forms for feasibility, safety, and economic analysis.

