### Data analysis

To evaluate the feasibility and safety of the TARGeT program for post-stroke survivors, we want to test the hypothesis that participants complied with the therapy plan and confirm that no major safety-related incidents occurred and concerns are raised. Studies exploring the unsupervised training with single devices found high adherence to the therapy plan (training on at least 80% of the days [18] and for at least 30 minutes [10,18]). We expect that training with a set of technologies at home will yield similar results. For this, we will perform descriptive analyses on the adherence to the therapy plan, i.e., we will analyze the attendance data (days trained out of six weeks) and the training dose (total time trained per day relative to therapy plan). Also, we will investigate whether financial resources (monthly household income) correlate with adherence. Moreover, we will analyze the journal and report forms of the participants, caregivers, clinicians, and technical personnel (frequency and type of concern (technical, general)), and the semi-structured interview data post-intervention by clustering according to safety and feasibility concerns.

Building on previous experiences [10,18,28], we hypothesize that the selected set of technologies is highly usable also in an unsupervised setting and that the user experience of the intervention is predominantly positive from participants and therapists. To evaluate the usability, we will analyze the SUS descriptively as well as the quantitative part of the semi-structured interviews post-intervention and perform a thematic analysis of the qualitative part of the interview. For the user experience, RawTLX and the interview data will be evaluated accordingly. Additionally, therapists’ expectations and perceived benefits will be determined by a descriptive and content analysis of the respective interview parts.

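### Attendance counts log-in days out of six weeks with no allowance for unusable equipment, so it measures programme feasibility rather than the participant compliance it is used to assess

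*Protocol article*

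**What the plan says.** Under Technology data, the article bases feasibility on adherence, made up of attendance and training dose. The numerator of attendance is fixed there: "Attendance is defined as daily access to the technologies, measured through log-in and log-out times recorded by the technologies". The denominator is fixed under Data analysis: "we will analyze the attendance data (days trained out of six weeks". Dose is the time trained per day relative to the therapy plan. Neither section sets aside days on which a device was out of order.

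The hypothesis attached to these measures is about the participants: "we want to test the hypothesis that participants complied with the therapy plan". Beside it stands a reference from earlier single-device studies, "training on at least 80% of the days [18] and for at least 30 minutes [10,18", with the expectation of similar results here. The method is descriptive: "we will perform descriptive analyses on the adherence to the therapy plan".

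Faults are recorded. The Intervention phase section states: "Any off-protocol contact required due to, e.g., non-training or technical issues of the technologies will be recorded in dedicated report forms". Journal and report forms also collect technical concerns from participants, caregivers, therapists and technical staff. Data analysis summarises these by frequency and by type (technical or general). It does not say that they will be matched to untrained days.

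**The concern.** A day on which neither device of the current set works produces no log-in. Under the stated definitions it scores exactly as a day on which the participant had working equipment and did not train. The resulting number describes how well participant and equipment performed together, while the hypothesis names the participant alone.

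The distinction matters for what the study is meant to inform. The Discussion says the results will show whether a powered randomised trial is feasible and necessary. A shortfall caused by equipment calls for work on the devices and technical support. A shortfall caused by participants calls for work on motivation, scheduling or the burden of the plan. A single attendance percentage cannot tell these apart, and a separate count of technical concerns does not show how many days each concern cost or for whom.

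**Working it through.** **Inputs**
- Numerator: days with a device log-in (Technology data).
- Denominator: six weeks (Data analysis), read here as 6 × 7 = 42 days because training is daily.
- Reference: 80% of days and 30 minutes (Data analysis).
- Daily plan: 15 minutes MyoGuide plus 45 minutes robot, extendable (Intervention phase).
- Days lost to faults, *k*: not given anywhere, so *k* is an assumption and is shown as a range. There is no figure of the plan's own to reproduce on this point.

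**Cost of one fully lost day.** 1/42 = 2.4 percentage points.

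**Days needed for 80%.** 0.80 × 42 = 33.6, so 34 days. That leaves 42 − 34 = 8 days that may be missed for any reason.

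**Share of usable days needed to reach 34 days, 34/(42 − *k*)**

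| Fully lost days *k* (assumed) | Usable days | Share needed | Score of someone who trains on every usable day, (42 − *k*)/42 |
|---|---|---|---|
| 0 | 42 | 81.0% | 100% |
| 3 | 39 | 87.2% | 92.9% |
| 5 | 37 | 91.9% | 88.1% |
| 7 | 35 | 97.1% | 83.3% |
| 9 | 33 | not reachable | 78.6% |

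**Example with *k* = 5.** A participant who trains on 33 of the 37 usable days has 33/37 = 89.2% on usable days but 33/42 = 78.6% on the stated denominator.

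**Chance of reaching 80%.** Assume a 90% chance of training on each usable day, with days independent. The probability of at least 34 days is 0.98 for *k* = 0, 0.67 for *k* = 4 and 0.29 for *k* = 6. With usable days as the denominator, the probability of reaching 80% is 0.98, 0.97 and 0.98.

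**One device fails, the other works.** The article does not say whether access to one device is enough for an attendance day. If it is, the day survives and the loss moves to dose. Suppose the participant completes the remaining part of the 60-minute plan and no more:
- Robot out: 15/60 = 25% of plan, below the 30-minute reference.
- MyoGuide out: 45/60 = 75% of plan.

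Measured against what could be done that day, both are 100% (15/15 and 45/45).

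**The case against.** The strongest reply is that all-cause attendance is the right measure. Technology data presents adherence as a measure of the feasibility of the programme, and in unsupervised home training equipment failure is part of feasibility. Removing fault days from the only measure would flatter the programme. This stands, and it is why the present measure should be kept. It does not answer the compliance hypothesis in Data analysis.

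Second, equipment problems are not concealed. Report forms are themselves primary outcomes, and technical concerns are analysed in the same paragraph as attendance. This also stands. What is unstated is the link from a concern to the days it cost.

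Third, a day-level coding rule may sit in the full protocol or the analysis plan, which are not shown. That is possible. The article nevertheless fixes a numerator, a denominator and a hypothesis, and as stated they do not match.

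A reader might infer more than the documents support:
- **That days with a network or sync failure are scored as untrained.** Log-in times are recorded by the devices, and the 4G link carries them to the servers. The website is tied to the contact rule, triggered by "no training with the technologies on the remote monitoring website for at least two consecutive days". A sync failure could prompt an unnecessary call, but nothing says that it loses an attendance day.
- **That the planned correlation of income with adherence is distorted.** No reason is given why faults would vary with income. Faults unrelated to income would mainly add noise.
- **That 80% is a pass mark.** It is a finding of earlier studies set beside a descriptive analysis. Whether those studies excluded fault days cannot be seen from the article.

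**Conclusion.** The point holds as a mismatch between measure and hypothesis. Log-in days out of six weeks, and dose relative to plan, describe the programme. They do not isolate whether participants complied, because days or minutes lost to equipment count the same as those a participant chose not to use.

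The size cannot be established from the article, since no fault rate is stated. The figures rest on reading six weeks as 42 days and on assumed counts of days with no usable device. If faults are rare the two measures will nearly coincide. A few lost days per participant would be enough to move a compliant participant across the descriptive 80% reference. No formal decision depends on that reference, so the consequence is for interpretation and for planning the next trial. The change is worth making but does not threaten the study.

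**What to change.** In Data analysis:
1. Keep days trained out of six weeks, and dose relative to plan, and label them as the programme-feasibility measures.
2. Using the report forms already collected, date-match technical problems to untrained or short days. Add days trained out of days with usable equipment, and the matching dose relative to what the working devices allowed, as the participant-compliance measures.
3. Report the number of fault days per participant, separating days with no usable device from days with one device out.
4. Describe the compliance hypothesis with the second pair of measures, and show the income correlation on both.
5. State whether access to one device or to both is needed for an attendance day.

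The cost is small: cross-referencing existing forms and adding columns to the adherence table. Complete analyses are planned only after data collection ends, so no new data collection is needed. The downside is some judgement in coding days, which is best limited by writing down the coding rule before adherence is tabulated.
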